#### 6.4.2.3 For subjects for whom donor leukocytes are not available after a minimum of 4 weeks of treatment in the stage 1 phase

- In the absence of active grade II-IV GVHD or de novo grade III-IV, or progression of cGVHD requiring new systemic treatment or increased doses of current systemic treatment, the subject will continue the same dose of IFN- $\gamma$  he or she is currently tolerating three times a week for two more weeks
- Then, IFN- $\gamma$  will be reduced to once weekly to complete a total of 12 weeks of therapy measured from the time of the first dose of IFN- $\gamma$ .

## 6.5 Protocol Visit, Monitoring, and Biospecimen Collection

### 6.5.1 Protocol Visits for Cohort 1

#### 6.5.1.1 Pre-treatment bone marrow aspirates for research (within two weeks before IFN- $\gamma$ administration)

- **Bone marrow aspirates** (no biopsy) will be performed for morphology, flow cytometry, and research sample (10mL) if the bone marrow research sample is not collected within two weeks before the first dose of IFN- $\gamma$ . The bone marrow aspirate for research can be performed concurrently with protocol visit #1, the first dose of IFN- $\gamma$ .

#### 6.5.1.2 Protocol visit #1: Stage 1, the first dose of IFN- $\gamma$

- Pre-treatment assessment (bone marrow aspirates, vital signs, and clinical assessment) as described in 6.3.1 will be performed before IFN- $\gamma$  administration.
- **Bone marrow aspirates** (no biopsy) will be performed for morphology, flow cytometry, and research sample (10mL) if the bone marrow research sample is not collected within two weeks before the first dose of IFN- $\gamma$ .
- Research sample collection: A bone marrow aspirate with a goal of 10 mL collected (in 10ml green top heparin tube x 1) and 30 mL of peripheral blood (10 mL green top heparin tube x 3 tubes) will be obtained as a baseline sample before IFN- $\gamma$  administration.
- First dose of IFN- $\gamma$  will be administered after the safety assessment.
- As described in 6.3.1., the patient will receive the training for self-injection of IFN- $\gamma$
- Safety monitoring: Subjects will be assessed for an acute reaction to the IFN- $\gamma$  or complication of biospecimen collection. Subjects will stay in the clinic for at least 1 hour after IFN- $\gamma$  administration and be assessed by a physician, physician assistant, advanced practice nurse or nurse prior to discharge from the clinic.

#### 6.5.1.3 Protocol visit #2: Stage 1, minimally 48 hours (up to one week) after the first dose of IFN- $\gamma$ : Safety and biological assessment of IFN- $\gamma$ , bone marrow aspiration for research

- Clinical safety monitoring: Any reaction or symptoms related to the prior doses of IFN- $\gamma$  and will be assessed specifically focusing on active grade II-IV GVHD or de novo grade III-IV, or progressive chronic GVHD
- **Bone marrow aspirates** (no biopsy) will be performed for morphology, flow cytometry, and research sample (10mL).
- Research sample collection: 10mL of bone marrow (10ml green top heparin tube), 30 mL of peripheral blood (10 mL green top heparin tube x 3 tubes) will be collected.
- The subsequent doses of IFN- $\gamma$  will be administered after the safety assessment.

6.5.1.4 Protocol visit #3: Stage 1, Day +14 ( $\pm$  5 days) after the first dose of IFN- $\gamma$ : Safety assessment of IFN- $\gamma$

- Clinical safety monitoring: Any reaction or symptoms related to the prior doses of IFN- $\gamma$  and will be assessed specifically focusing on active grade II-IV GVHD or de novo grade III-IV, or progressive chronic GVHD
- Laboratory monitoring: CBC with differential, chemistry panel (Na, K, Cl, CO2, creatinine, glucose, urea nitrogen, phosphorus, magnesium, albumin, calcium, LDH, uric acid), hepatic (alkaline phosphatase, ALT, AST, and total bilirubin ) panel
- The subsequent doses of IFN- $\gamma$  will be administered after safety assessment.

6.5.1.5 Protocol visit #4: End of stage 1 and pre-treatment evaluation for stage 2 (donor lymphocyte infusion), day +28 ( $\pm$  5 days) after the first dose of IFN- $\gamma$  or two weeks ( $\pm$  5 days) after a stable dose of IFN- $\gamma$ :

- Clinical safety monitoring: Any reaction or symptoms related to the prior doses of IFN- $\gamma$  and will be assessed specifically focusing on active grade II-IV GVHD or de novo grade III-IV, or progressive chronic GVHD
- Laboratory monitoring: CBC with differential, chemistry panel (Na, K, Cl, CO2, creatinine, glucose, urea nitrogen, phosphorus, magnesium, albumin, calcium, LDH, uric acid), hepatic (alkaline phosphatase, ALT, AST, and total bilirubin) panel
- STR chimerism of bone marrow (if collected) and peripheral blood (whole blood, or CD3 and myeloid)
- **Bone marrow aspirates** (no biopsy) will be performed for morphology, flow cytometry, and research sample (10mL). Cytogenetics/molecular testing only needed if clinically indicated to follow MRD.
- Research sample collection: 10mL of bone marrow (10mL green top heparin tube), 30 mL of peripheral blood (10 mL green top heparin tube x 3 tubes) will be collected.
- The subsequent doses of IFN- $\gamma$  will be administered after the safety assessment.
- If DLI is available, the first dose of DLI will be infused within two weeks from this visit.

6.5.1.6 Protocol visit #5: Stage 2 first safety assessment, 14 days (+/- 5 days) after the first dose of DLI, or two weeks (+/- 5 days) after the end visit of the first stage for non-DLI subjects.

- Clinical safety monitoring: Any reaction or symptoms related to the IFN- $\gamma$  or DLI will be assessed, specifically focusing on active grade II-IV GVHD or de novo grade III-IV, or progressive chronic GVHD
- Laboratory monitoring: CBC with differential, chemistry panel (Na, K, Cl, CO2, creatinine, glucose, urea nitrogen, phosphorus, magnesium, albumin, calcium, LDH, uric acid), hepatic (alkaline phosphatase, ALT, AST, and total bilirubin) panel
- The subsequent frequency IFN- $\gamma$  will be reduced to once-weekly dosing for four more weeks.

6.5.1.7 Protocol visit #6: Stage 2 follow up safety assessment, 28 days (+/- 5 days) after the first dose of DLI, or 28 days (+/- 5 days) after the end visit of the first stage for non-DLI subjects

- Clinical safety monitoring: Any reaction or symptoms related to the IFN- $\gamma$  or DLI will be assessed, specifically focusing on active grade II-IV GVHD or de novo grade III-IV, or progressive chronic GVHD
- Laboratory monitoring: CBC with differential, chemistry panel (Na, K, Cl, CO2, creatinine, glucose, urea nitrogen, phosphorus, magnesium, albumin, calcium, LDH, uric acid), hepatic (alkaline phosphatase, ALT, AST, and total bilirubin) panel
- Research sample collection: 30 mL of peripheral blood (10 mL green top heparin tube x 3 tubes) will be collected.
- Optional bone marrow aspirates (no biopsy) will be performed for morphology, flow cytometry, and research sample (10ml) if clinically indicated. Cytogenetics/molecular testing only needed if clinically indicated to follow MRD if clinically indicated.
- If the second or third dose of DLI is available, the DLI will be infused at minimal 4 weeks of interval in the absence of active grade II-IV GVHD or de novo grade III-IV, or progressive chronic GVHD requiring new treatment or increased doses of current treatment per treating physician's determination.
- There is an optional bone marrow aspirate if clinically indicated before the second or the third DLI per the treating physician, and research sample (10mL in green top heparin tube) will be collected.

6.5.1.8 Protocol visit #7: Stage 2, end of IFN- $\gamma$  therapy assessment

- At the 28 days (+/- 5 days) after the last dose of DLI, or eight weeks (+/- 5 days) after the end visit of the first stage for non-DLI subjects
- Clinical safety monitoring: Any reaction or symptoms related to the IFN- $\gamma$  or DLI will be assessed, specifically focusing on active grade II-IV GVHD or de novo grade III-IV, or progressive chronic GVHD
- Laboratory monitoring: CBC with differential, chemistry panel (Na, K, Cl, CO2, creatinine, glucose, urea nitrogen, phosphorus, magnesium, albumin, calcium, LDH, uric acid), hepatic (alkaline phosphatase, ALT, AST, and total bilirubin) panel
- STR chimerism of bone marrow (if available) and peripheral blood (CD3 and myeloid)
- **Bone marrow aspirates** (no biopsy) will be performed for morphology, flow cytometry, and research sample (10mL). Cytogenetics/molecular testing only needed if clinically indicated to follow MRD within 3 days after the last dose of IFN- $\gamma$
- Research sample collection: 10mL of bone marrow (10ml green top heparin tube), 30 mL of peripheral blood (10 mL green top heparin tube x 3 tubes) will be collected.
- The date of the last dose of IFN- $\gamma$  will be recorded.

6.5.1.9 Protocol visit #8: 28 days (+/- 5 days) safety assessment after the last dose of IFN- $\gamma$  therapy (Off treatment assessment)

- Clinical safety monitoring: Any reaction or symptoms related to the IFN- $\gamma$  or DLI will be assessed, specifically focusing on active grade II-IV GVHD or de novo grade III-IV, or progressive chronic GVHD. Monitoring of adverse events annotated to IFN- $\gamma$  therapy will be completed on this off-treatment assessment visit
- Laboratory monitoring: CBC with differential, chemistry panel (Na, K, Cl, CO2,

creatinine, glucose, urea nitrogen, phosphorus, magnesium, albumin, calcium, LDH, uric acid), hepatic (alkaline phosphatase, ALT, AST, and total bilirubin) panel

- Research sample collection: 30 mL of peripheral blood (10 mL green top heparin tube x 3 tubes) will be collected.

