#### 6.4.2 Dose and schedule of IFN- $\gamma$ during the donor lymphocyte infusion stage

##### 6.4.2.1 For the subjects for whom donor leukocytes are available (cohort 1)

- After the first dose of DLI, the same dose of IFN- $\gamma$  as used pre-DLI for that patient will be continued three times a week for four weeks. If the subject develops intolerance to IFN- $\gamma$  during this period, we will reduce the frequency of IFN- $\gamma$  to once weekly.
- Four weeks after the first dose of DLI, the frequency of IFN- $\gamma$  will be tapered to once weekly, continued until the next DLI.
- A minimum of four weeks after the first dose of DLI, the subject will receive the second DLI, in the absence of active grade II-IV GVHD or de novo grade III-IV, or progressive chronic GVHD requiring new systemic treatment or increased doses of current systemic treatment per treating physician's determination. IFN- $\gamma$  will be continued at the same dose once weekly. There is an optional bone marrow aspirate if clinically indicated prior to the second DLI per the treating physician, and a research sample can be collected at that time.
- A minimum of 4 weeks after the second DLI, the subject will receive the third dose of DLI, in the absence of active grade II-IV GVHD or de novo grade III-IV, or progressive chronic GVHD defined by a requirement for new systemic treatment or increased doses of current systemic treatment. IFN- $\gamma$  will be continued at the same dose once weekly for

four more weeks. There is an optional bone marrow aspirate if clinically indicated before the third DLI, and a research sample may also be collected at that time.

- IFN- $\gamma$  will be continued once weekly until four weeks of the last dose of DLI or 12 weeks after the first dose of IFN- $\gamma$  whichever occurs later. If the subject develops intolerance to IFN- $\gamma$  during this period, we will discontinue IFN- $\gamma$
- At the end IFN- $\gamma$  treatment, the bone marrow aspirate is required ideally within seven days after the last dose of IFN- $\gamma$

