**Genital tract:**

- Female: Vaginitis / stricture: pain, ulceration, inflammation, eventually scarring / narrowing of the vaginal opening.
- Male: Pain, burning sensation, lichen planus or lichen sclerosis features, scarring, stenosis.

If any genital tract abnormalities were present, but explained entirely by non-GVHD causes, specify documented causes.

### 15.3 Appendix C. Schedule of event for cohort 1

|                                                                                                    | Screening | Stage 1 |    |      | Stage 2 |      |      |      |      |       |
|----------------------------------------------------------------------------------------------------|-----------|---------|----|------|---------|------|------|------|------|-------|
| Visit                                                                                              | Pre       | V1      | V2 | V3   | V4      | V5   | V6   | V7   | V8   | V9    |
| Days                                                                                               | -14 to -1 | 0       | 2  | 14   | 28      | 42   | 56   | 84   | 112  | 180   |
| Window (days)                                                                                      |           |         | +5 | +/-5 | +/-5    | +/-5 | +/-5 | +/-5 | +/-5 | +/-14 |
| Enrollment procedure                                                                               |           |         |    |      |         |      |      |      |      |       |
| Eligibility assessment                                                                             | X         |         |    |      |         |      |      |      |      |       |
| Informed consent                                                                                   | X         |         |    |      |         |      |      |      |      |       |
| Pre-treatment assessment                                                                           |           |         |    |      |         |      |      |      |      |       |
| H&P, performance status                                                                            | X         |         |    |      |         |      |      |      |      |       |
| History of GVHD                                                                                    | X         |         |    |      |         |      |      |      |      |       |

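### Cohort 1, one DLI: section 6.5.1.8 dates the end-of-IFN-γ visit (#7) on the same day as visit #6, contradicting section 6.4.2.1 and Appendix C

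*Protocol*

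**What the plan says.** All of this concerns cohort 1.

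- **Visit #6 (6.5.1.7):** "Protocol visit #6: Stage 2 follow up safety assessment, 28 days (+/- 5 days) after the first dose of DLI".
- **Visit #7 (6.5.1.8), DLI patients:** "At the 28 days (+/- 5 days) after the last dose of DLI". For patients without DLI it is "eight weeks (+/- 5 days) after the end visit of the first stage for non-DLI subjects". The visit's title makes it the end-of-IFN-γ assessment. It includes the examination, laboratory panel, chimerism, marrow and research samples, refers to three days after the last IFN-γ dose, and records the date of that dose.
- **End of IFN-γ (6.4.2.1):** the drug "will be continued once weekly until four weeks of the last dose of DLI or 12 weeks after the first dose of" IFN-γ, whichever is later. The same section requires a marrow at the end of treatment, ideally within seven days of the last dose.
- **Visit #8 (6.5.1.9):** 28 days (±5) after the last IFN-γ dose.
- **Timing of the first DLI (6.5.1.5):** visit #4 is the "End of stage 1 and pre-treatment evaluation for stage 2 (donor lymphocyte infusion), day +28" (±5 days), and "the first dose of DLI will be infused within two weeks from this visit".
- **Schedule table ("Appendix C. Schedule of event for cohort 1"):** V4 on day 28, V5 on 42, V6 on 56, V7 on 84, V8 on 112. V7 carries examination, laboratory panel, marrow and chimerism, with no exception for patients who have one DLI.

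**The concern.** Visit #6 counts from the first DLI and visit #7 from the last. When there is only one DLI, the first is also the last, and the two visits fall together. Visit #7 then cannot do what its title and content require, because injections are still due under section 6.4.2.1 and there is no last-dose date to record. Nor can a site be sure at DLI + 28 days that the DLI was the last, since section 6.4.2.1 sets a minimum interval to the next DLI but no maximum.

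The one-DLI patient is not a rare exception. The cohort 1 goal (Synopsis; section 8.2.1) is at least three patients with at least one DLI, out of an expected six and probably no more than nine, so one DLI is enough to count.

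Two things are at stake. The first is whether an examination and laboratory panel are held around the true end of IFN-γ, when adverse events under IFN-γ plus DLI are a primary safety endpoint. The second is whether end-of-therapy marrow and chimerism are read at the same point in one-DLI and no-DLI patients. With so few patients, one or two read at a different time affects any summary.

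**Working it through.** This is calendar arithmetic on the protocol's own anchors. Day 0 is the first IFN-γ dose, and d is the day of the first DLI.

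**Formulas**
- V6 = d + 28 (6.5.1.7)
- V7 = last DLI + 28 (6.5.1.8)
- End of IFN-γ: E = later of (last DLI + 28) and day 84 (6.4.2.1)
- V8 = E + 28 (6.5.1.9)
- d = 28 to 42, from visit #4 on day 28 plus up to two weeks (6.5.1.5)

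**Reproducing Appendix C (V6 56, V7 84, V8 112)**
- Two DLIs, days 28 and 56: V6 = 28 + 28 = 56; V7 = 56 + 28 = 84; E = 84; V8 = 112. This agrees.
- No DLI: V7 = 28 + 56 = 84. This agrees.
- One DLI on day 28: V6 = 56 and V8 = 84 + 28 = 112 agree, but V7 = 28 + 28 = 56, not 84.

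**One DLI, target days**

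| DLI day | V6 | V7 by 6.5.1.8 | E | V7 before E | V8 | V7 to V8 |
|---|---|---|---|---|---|---|
| 28 | 56 | 56 | 84 | 4 weeks | 112 | 8 weeks |
| 35 | 63 | 63 | 84 | 3 weeks | 112 | 7 weeks |
| 42 | 70 | 70 | 84 | 2 weeks | 112 | 6 weeks |
| 56 | 84 | 84 | 84 | 0 | 112 | 4 weeks |

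The last row is a patient whose stage 1 was extended by two weeks after a frequency reduction (6.3.2), with visit #4 near day 42 and the DLI up to two weeks later. The early timing is gone, but V6 and V7 still coincide.

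**Effect of windows.** With a DLI on day 28, V7 may fall on days 51 to 61 and V8 on days 107 to 117. The gap is 107 − 61 = 46 to 117 − 51 = 66 days, or 6.6 to 9.4 weeks.

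**Two further disagreements on when IFN-γ ends**
- The visit #5 text (6.5.1.6, DLI + 14 days) reduces IFN-γ to weekly for four more weeks, which implies an end at d + 14 + 28 = d + 42. For d = 28 that is day 70 rather than 84. V7 would still be two weeks early, and V8 (day 98) six weeks after it.
- Three DLIs on days 28, 56 and 84: 6.4.2.1 gives E = 84 + 28 = 112 and 6.5.1.8 gives V7 = 112, while Appendix C has V7 on day 84.

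**The case against.** The strongest reply is that the protocol as a whole shows when visit #7 belongs. Its title, its recording of the last-dose date, the marrow timing in 6.4.2.1, the Synopsis (repeat marrow after the 12-week course) and Appendix C all point to the end of IFN-γ. On this view the day-56 reading isolates one line, and a careful site would not follow it. Much of that stands: the defect is one date line that contradicts the rest. But that line is the operative timing instruction in the visit section, and it carries its own ±5-day window, so different sites could reasonably act differently.

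A reader might infer more: that the protocol leaves one-DLI patients without any safety visit or laboratory panel for eight weeks, so that events go unseen and the primary safety endpoint is understated. The documents do not support this. Appendix C schedules the day-84 visit. Section 2.2 says GVHD is routinely monitored in all transplant recipients. Section 9.1 has all observed or volunteered events recorded, and section 9.5 continues collection to visit #8. The four- and eight-week figures are also not general, since they require a DLI on day 28.

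Prospective reach may be limited too. The Synopsis describes monotherapy safety as already confirmed in the first cohort. Cohort 2's visit #7 (6.5.2.8) is anchored at 12 weeks after the first IFN-γ dose, so it does not share the fault. The protocol does not say whether any cohort 1 patient is still on treatment.

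**Conclusion.** The point holds as an internal contradiction. For every cohort 1 patient with one DLI, section 6.5.1.8 gives visit #7 the same target day as visit #6, whatever the DLI day. Where the DLI falls on days 28 to 42 and the 6.5.1.8 line is followed, visit #7 comes two to four weeks before IFN-γ ends under 6.4.2.1, and six to eight weeks pass before the next section 6.5.1 visit. End-of-therapy marrow and chimerism would be taken at days 56 to 70 rather than day 84 as in no-DLI patients. Under Appendix C none of this occurs.

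The figures are target days. They assume visit #4 on day 28, no extension of stage 1, IFN-γ completed as planned and the end rule of 6.4.2.1. Bias in the safety endpoint is possible but not shown. The point deserves correction because the change is small and one-DLI patients count towards the cohort goal.

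**What to change.** 1. In 6.5.1.8, replace the last-DLI anchor for visit #7 with the actual end of IFN-γ, and state that it is a separate visit from #6.
2. Reconcile 6.4.2.1, the visit #5 text in 6.5.1.6, section 6.5.1.8 and Appendix C on when IFN-γ ends, including for patients with a third DLI. Which duration is right is for the investigators; this review takes no position.
3. For cohort 1 patients already treated, report the actual visit #7 date relative to the last IFN-γ dose beside the end-of-therapy marrow and chimerism results.

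The first change is one sentence. For a one-DLI patient it adds no visit, marrow or sample beyond Appendix C. The second is a short text reconciliation, and the third uses dates the protocol already has recorded.

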Cohort 2: As we confirmed the safety of IFN- $\gamma$  monotherapy in the first cohort, we will evaluate a second cohort wherein we will shorten IFN- $\gamma$  monotherapy (stage 1) to 1 week before DLI. In stage 1, we will assess the safety a fixed-dose of IFN- $\gamma$  (100mcg subcutaneously three times per week) for one week. The bone marrow biopsies will be performed before and no earlier than 48 hours to 1 week after the first dose of IFN- $\gamma$  to assess malignant blasts for an IFN- $\gamma$  response. In stage 2, subjects who have tolerated IFN- $\gamma$  will receive DLI in a dose-escalating manner. IFN- $\gamma$  will be continued three times a week for seven weeks after the first dose of DLI, followed by once-weekly IFN- $\gamma$  for four weeks. The patients will be off treatment after a 12 week-course of IFN- $\gamma$  with a repeat bone marrow biopsy at this point. The clinical outcomes will be monitored at six months after the first dose of IFN- $\gamma$  and then the subjects will be off study. Figure 2 summarizes the study design for cohort 2.

Sample size: Our goal is to have at least three patients receive at least one dose of DLI. For example, if the first three patients all complete stage 1 and stage 2, this initial pilot study would be completed with three patients. We estimate enrolling six total patients, but not likely more than nine, as some patients may not be able to complete the study due to the development of rapid disease progression or unavailability of DLI. Based on the nature of the transplant populations at our centers, we estimate accrual will be completed within six months.

For cohort 2, we aim to enroll six patients receiving IFN- $\gamma$  and at least one dose of DLI.

[figure not shown]

**Figure 1. Study Design of Cohort 1:** The figure outlines the scheme of how to administer IFN- $\gamma$  and subsequent donor lymphocyte infusions after enrollment. Biospecimens will also be collected, as shown. BM: bone marrow aspirates, DLI: donor lymphocyte infusion, IFN- $\gamma$ : interferon-gamma, PBMC: peripheral blood mononuclear cells

[figure not shown]

**Figure 2. Study Design of Cohort 2:** The figure outlines the scheme of how to administer IFN- $\gamma$  and subsequent donor lymphocyte infusions after enrollment. Biospecimens will also be collected, as shown. BM: bone marrow aspirates, DLI: donor lymphocyte infusion, IFN- $\gamma$ : interferon-gamma, PBMC: peripheral blood mononuclear cells

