#### 6.4.2.2 For the subjects for whom donor leukocytes are available (cohort 2)

- After the first dose of DLI, the same dose of IFN- $\gamma$  as used pre-DLI for that patient will be continued three times a week for four weeks. If the subject develops intolerance to IFN- $\gamma$  during this period, we will reduce the frequency of IFN- $\gamma$  to once weekly.
- A minimum of four weeks after the first dose of DLI, the subject will receive the second DLI, in the absence of active grade II-IV GVHD or de novo grade III-IV, or progressive chronic GVHD requiring new systemic treatment or increased doses of current systemic treatment per treating physician's determination. IFN- $\gamma$  will be continued at the same dose three times weekly. There is an optional bone marrow aspirate if clinically indicated prior to the second DLI per the treating physician, and a research sample can be collected at that time.
- 8 weeks after the first dose of IFN- $\gamma$  (or approximately 7 weeks after the first dose of DLI), the frequency of IFN- $\gamma$  will be tapered to once weekly, continued until the next DLI.
- A minimum of 4 weeks after the second DLI, the subject will receive the third dose of DLI, in the absence of active grade II-IV GVHD or de novo grade III-IV, or progressive chronic GVHD defined by a requirement for new systemic treatment or increased doses of current systemic treatment. IFN- $\gamma$  will be continued at the same dose once weekly for three more weeks. There is an optional bone marrow aspirate if clinically indicated before the third DLI, and a research sample may also be collected at that time.
- IFN- $\gamma$  will be continued once weekly until four weeks of the last dose of DLI or 12 weeks after the first dose of IFN- $\gamma$  whichever occurs later. If the subject develops intolerance to IFN- $\gamma$  during this period, we will discontinue IFN- $\gamma$
- At the end IFN- $\gamma$  treatment, the bone marrow aspirate is required ideally within seven days after the last dose of IFN- $\gamma$

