| Donor lymphocyte infusion                                                                          |           |         |    |      | X       |      | X*2) | X*3) |      |       |
| Research sample collection                                                                         |           |         |    |      |         |      |      |      |      |       |
| Bone marrow aspirate (10mL)                                                                        | X*1)      | X*1)    | X  |      | X       |      |      | X    |      | X*4)  |
| Peripheral blood (30ml)                                                                            |           | X       | X  |      | X       |      | X    | X    | X    | X     |
| *1) No need to repeat bone marrow if the research sample was collected during the screening period |           |         |    |      |         |      |      |      |      |       |
| *2) Only applicable if the second dose of DLI is feasible                                          |           |         |    |      |         |      |      |      |      |       |
| *3) Only applicable if the third dose of DLI is feasible                                           |           |         |    |      |         |      |      |      |      |       |
| *4) This bone marrow is optional and can be collected if clinically indicated.                     |           |         |    |      |         |      |      |      |      |       |

## 15.4 Appendix D. Schedule of event for cohort 2

|                                                                                                    | Screening | Stage 1 |    | Stage 2  |      |      |      |       |       |       |
|----------------------------------------------------------------------------------------------------|-----------|---------|----|----------|------|------|------|-------|-------|-------|
| Visit                                                                                              | Pre       | V1      | V2 | V3       | V4   | V5   | V6   | V7    | V8    | V9    |
| Days                                                                                               | -14 to -1 | 0       | 2  | 7        | 21   | 35   | 56   | 84    | 112   | 180   |
| Window (days)                                                                                      |           |         | +5 | -3 to +5 | +/-5 | +/-5 | +/-7 | +/-14 | +/-14 | +/-28 |

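### The rules for when IFN-γ ends and when the end-of-therapy visit (V7) takes place conflict: in cohort 1 for one and for three donor lymphocyte infusions, in cohort 2 for three

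*Protocol*

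**What the plan says.** **Cohort 1, visits.** Section 6.5.1.7 defines V6 as "Stage 2 follow up safety assessment, 28 days (+/- 5 days) after the first dose of DLI". Section 6.5.1.8 defines V7, titled as the end-of-IFN-γ assessment, by the last DLI: "At the 28 days (+/- 5 days) after the last dose of DLI". For patients without DLI the same line counts eight weeks from the end of stage 1. Section 6.5.1.5 says of DLI #1: "If DLI is available, the first dose of DLI will be infused within two weeks from this visit".

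**Cohort 1, stopping.** Section 6.4.2.1 says that IFN-γ "will be continued once weekly until four weeks of the last dose of DLI or 12 weeks after the first dose of" IFN-γ, whichever is later, and that "the bone marrow aspirate is required ideally within seven days after the last dose of" IFN-γ. After a third DLI it asks for four more weekly doses. The synopsis ends treatment, with a repeat marrow, after a 12-week course.

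**Cohort 1, Appendix C.** V6 is day 56, V7 day 84 ± 5 and V8 day 112 ± 5. The DLI row has marks at V4, V6 and V7. The footnote to the V7 mark reads "3) Only applicable if the third dose of DLI is feasible". IFN-γ is marked through V6 and not afterwards.

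**Cohort 2.** After DLI #3, one bullet of Section 6.4.2.2 says that IFN-γ "will be continued at the same dose once weekly for three more weeks". The next repeats the later-of rule from cohort 1. Section 6.5.2.8 places V7 at 12 weeks ± 2 weeks after the first dose.

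**The concern.** V7 carries the required end-of-therapy marrow. It is the natural reading for the secondary endpoint of blast reduction after IFN-γ and DLI (Section 1.2.3). Section 2.4 would treat any significant reduction as reasonable evidence for efficacy.

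If Section 6.5.1.8 is followed to the letter, a one-DLI patient who stays on IFN-γ has this marrow with about four weekly doses still to come. It then cannot lie within seven days after the last dose, as Section 6.4.2.1 asks. If Appendix C is followed for three DLIs, the end-of-therapy marrow is taken on the day of DLI #3. In cohort 2, the stop date of an investigational drug depends on which of two adjacent bullets the site applies.

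**Working it through.** **Inputs.** Day 0 is the first IFN-γ dose. Appendix C gives cohort 1 DLIs nominally on days 28, 56 and 84. In cohort 2, DLI #1 is nominally on day 7 and later DLIs follow at the four-week minimum (days 35 and 63).

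**Formulas, cohort 1.**
- V6 (6.5.1.7) = first DLI + 28
- V7 (6.5.1.8) = last DLI + 28
- End of IFN-γ (6.4.2.1) = max(last DLI + 28, 84)
- V8 (6.5.1.9) = last dose + 28

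**Appendix C's day 84, reproduced.** It follows for two DLIs: 56 + 28 = 84 and max(84, 84) = 84. It also follows with no DLI: 28 + 56 = 84. It does not hold for one or three.

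| DLIs | V7 by 6.5.1.8 | End of IFN-γ by 6.4.2.1 | V7 in Appendix C |
|---|---|---|---|
| 1 | 28 + 28 = 56 | max(56, 84) = 84 | 84 |
| 2 | 56 + 28 = 84 | max(84, 84) = 84 | 84 |
| 3 | 84 + 28 = 112 | max(112, 84) = 112 | 84 |

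**One DLI.** The first DLI is also the last, so V6 and V7 coincide whatever its date. Nominally both fall on day 56, and 84 − 56 = 28 days, or four weekly doses.

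On the standard schedule V4 falls on days 23–33. With DLI #1 up to 14 days later, DLI #1 falls on days 23–47. The V7 window closes at DLI #1 + 28 + 5:
- DLI #1 on day 23: closes on day 56, which is 28 days before day 84
- DLI #1 on day 28: closes on day 61, 23 days before
- DLI #1 on day 47: closes on day 80, 4 days before

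Measured from the nominal V7 day instead, the gap is 28 days for DLI #1 on day 28, 14 days for day 42 and zero for day 56.

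**Three DLIs, cohort 1.** The two text sections agree on day 112. Appendix C's V7 (day 84) is then the day of DLI #3. Its V8 (day 112) is the day IFN-γ ends, whereas V8 by the text is 112 + 28 = day 140.

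**Cohort 2, DLI #3 on day D.** One bullet gives D + 21, the next max(D + 28, 84). Since D + 21 < D + 28 ≤ max(D + 28, 84), they never agree and differ by at least 7 days.
- Nominal, D = 7 + 28 + 28 = 63: day 84 against day 91, a difference of one weekly dose. Day 91 lies inside the V7 window, 84 ± 14 = days 70–98.
- The later-of date passes day 98 when DLI #1 + 56 + 28 > 98, that is, when DLI #1 is after day 14.
- DLI #1 on day 21 (nominal V3 plus two weeks): D = 77, end = day 105, which is 7 days past the window.
- With one or two DLIs at four-week spacing and DLI #1 as late as day 26 (latest V3, day 12, plus 14), max(54, 84) and max(82, 84) both give day 84. No overrun occurs.

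**The case against.** The intent can be recovered. V7's title, the seven-day marrow rule, the synopsis and Appendix C all point to the end of treatment, so for one DLI only the anchor in Section 6.5.1.8 is out of line. For three DLIs only the appendix lags. In cohort 2, the later-of bullet can be read as controlling, with three weeks as a minimum. This shows which rule to keep, but the text still gives sites conflicting instructions.

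The one-DLI conflict is also narrower than it looks, and this stands. DLI #2 may be withheld for GVHD, and Section 6.7 stops IFN-γ for new-onset grade 3 or 4 acute GVHD or for progression needing immediate therapy. Such a patient never runs to day 84. Section 6.5.1.5 also allows V4 two weeks after a stable dose, so a prolonged stage 1 can push DLI #1 to about day 56, where the rules agree. Even on the standard schedule, DLI #1 on day 46 or 47 gives a V7 window closing on day 79 or 80, which touches Appendix C's days 79–89. Depending on the weekly dosing day, the last dose could already have been given by then.

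A reader might infer from the synopsis that one-DLI patients are the typical case, because it says "Our goal is to have at least three patients receive at least one dose of DLI". That wording counts patients with one, two or three infusions alike. The documents do not show how many stop at one.

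A reader might also infer that the primary endpoint or adverse event collection is compromised. The primary biological comparison uses the pre-treatment and V2 marrows. V8 and Section 9.5 follow the last IFN-γ dose. The secondary endpoint names no visit, and Section 2.4 says that the study is not powered for efficacy.

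**Conclusion.** The text is wrong as written; the error is one of consistency, minor to moderate in weight.

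- **Cohort 1, exactly one DLI**, standard schedule, IFN-γ continued: V7 falls on the V6 day, nominally 28 days before treatment ends. Within the permitted DLI #1 dates its window closes 4 to 28 days before day 84.
- **Cohort 1, three DLIs:** the error is in Appendix C only, where both V7 and V8 are 28 days early.
- **Cohort 2, three DLIs:** the two stop dates differ nominally by one weekly dose, inside the V7 window. The later-of date passes that window only if DLI #1 is after day 14 and a third DLI is given.

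These figures assume four-week spacing of DLIs and, for the one-DLI case, V4 on days 23–33 with DLI #1 within two weeks. The synopsis reports that monotherapy safety was confirmed in cohort 1 but does not say that cohort 1 treatment is complete. If it is, the cohort 1 part governs only how its marrows are classified.

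**What to change.** 1. Make the later-of rule (four weeks after the last DLI or 12 weeks after the first IFN-γ dose) the single stop rule. Change the three-week bullet in Section 6.4.2.2 to match.
2. Anchor V7 in Sections 6.5.1.8 and 6.5.2.8 and in Appendices C and D to the actual end of IFN-γ. Use one marrow window, within seven days after the last dose. It replaces the three-day wording in 6.5.1.8 and the two-week wording in 6.5.2.8.
3. Remove DLI #3 from the V7 column of Appendix C, and let the nominal V8 day follow the last dose.
4. For DLI patients, delete or align with Section 6.4.2 the instruction at cohort 1 V5 (6.5.1.6) and cohort 2 V4 (6.5.2.5) to go to weekly dosing for four further weeks. Nominally it ends dosing on day 42 + 28 = 70 and day 21 + 28 = 49.
5. In Section 9.5, match the V8 window to each cohort (± 5 days in cohort 1, ± 2 weeks in cohort 2). Correct the reference to Section 6.5.9, which does not exist.
6. Classify marrows already taken by the actual date of the last IFN-γ dose. A one-DLI patient's day-56 marrow with treatment continuing is a V6 sample. A marrow on the day of DLI #3 is a pre-DLI #3 sample.

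The cost is amendment wording and two corrected appendices, with no new procedures. V8 still precedes V9 (day 180): day 140 for three DLIs in cohort 1, and 105 + 28 = day 133 in the late cohort 2 example.
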